### Statistical considerations

3.10

#### Sample size

3.10.1

For Aim 1, hypotheses will be tested with 80% power using 5% two-sided alpha Bonferroni corrected to 2.5% for two group comparisons. The primary outcome is the longitudinal daily cigarette count from baseline (days 1-5) to the end of the e-cigarette switch phase (day 49), with week 26 as a secondary endpoint. We based the power on data from prior switching studies. A sample of 210 (70 per group) will allow us to detect an overall standardized slope of 0.19. To account for a ∼15% attrition rate [67], we will enroll ∼ 240 participants to have 210 who complete the 26-week follow-up. We expect the initial and sustained switch for participants randomized to fruit-flavoring to be greater than for participants randomized to tobacco or menthol flavoring. A sample of 70 per group enables us to detect a difference of ∼3.73 cigarettes per day (CPD). We will also be able to detect a difference in slopes of 0.13 (CPD per day change).

For Aim 2, a sample of 70 per group will allow us to detect a between-group effect size of 0.5. For the relative reinforcing value of flavored e-cigarettes (RRVF), this means we can detect a difference in breakpoint of 2.0. Positive affect will be assessed as a difference score with a standard deviation of approximately 7.0, yielding 80% power to detect a difference of approximately 3.7. Subjective reward has a standard deviation of 1.3, which allows us to detect a 0.68 difference. In turn, the continuous measures of RRVF, positive affect, and subjective reward will be used to predict changes in mean cigarette counts from baseline to the end of the switch phase and from baseline to the 26-week follow-up. The sample of 210 allows us to detect a standardized slope of 0.2. The actual standard deviation for the cigarette consumption change score is 7.1. The detectable slopes are 0.37 for RRVF, 0.20 for positive affect, and 1.07 for subjective reward.

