## Abstract

While regulations have restricted the sale of pod-style fruit-flavored e-cigarettes, observational and clinical data suggest that their use is associated with smoking cessation among adults. Surprisingly, no randomized clinical trials have tested whether fruit flavors affect smoking outcomes compared with those authorized for sale, and, if so, why. Adults who smoke cigarettes daily, who have had multiple prior unsuccessful quit attempts, and who are interested in quitting smoking by switching to an e-cigarette will be recruited. Eligible adults will be randomized to fruit, menthol, or tobacco-flavored e-cigarettes. The baseline smoking rate will be established on days 1-5. Laboratory visits on days 6 and 7 will assess flavor-associated subjective reward and the reinforcing value of flavored e-cigarettes relative to combustible cigarettes. Participants will then receive an e-cigarette device and a 6-week supply of nicotine pods (5% nicotine) in their assigned flavor, and a structured action plan to quit smoking by switching to the e-cigarette. The primary outcome is the longitudinal daily cigarette count from baseline through the end of the six-week switch period (primary endpoint) and at the 26-week follow-up (secondary endpoint). Complete switching will be verified with a carbon monoxide value < 5 ppm. Secondary outcomes include subjective reward, relative reinforcing value, and positive affect. This trial will determine if fruit-flavored e-cigarettes facilitate initial and sustained switching more than menthol or tobacco, whether greater rewarding and positively reinforcing effects drive switching, and if the unavailability of fruit-flavoring may foster continued smoking for those unable to quit with FDA-approved medication.

This trial was registered at CT.gov (NCT06264154) https://clinicaltrials.gov/study/NCT06264154 on February 16, 2024.

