## Aims and hypotheses

2

The current study (NCT06264154) has two aims. Aim 1 seeks to evaluate the effects of fruit-flavored versus tobacco-flavored and menthol-flavored e-cigarettes on combustible cigarette smoking among adults who have persistently smoked. We hypothesize that participants randomized to fruit-flavored e-cigarettes will be more likely to switch from combustible cigarettes to e-cigarettes during the 6-week switch phase and at the 26-week follow-up than participants randomized to tobacco-flavored or menthol-flavored e-cigarettes. Complete switching, partial switching, and no switching will be measured. Aim 2 seeks to examine whether the rewarding and reinforcing effects of e-cigarette flavoring mediate switching behavior. We hypothesize that fruit-flavored e-cigarettes will produce greater subjective reward, relative reinforcing value, and positive affect than tobacco-flavored or menthol-flavored e-cigarettes. In turn, greater subjective reward, relative reinforcing value, and positive affect will predict fewer cigarettes smoked per day during the 6-week switch phase and at the 26-week follow-up.

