### Overview of study design

3.1

The proposed study will evaluate whether fruit-flavored (FF: watermelon and blueberry) versus traditional-flavored e-cigarettes [tobacco (TF) or menthol (MF)] more readily substitute for combustible cigarettes and if the rewarding and reinforcing effects of flavoring facilitate changes in smoking behavior among 210 adults who have persistently smoked cigarettes. Eligible adults will be randomly assigned 1:1:1 to FF (n = 70), TF (n = 70), or MF (n = 70) and participate in 9 visits across 26 weeks (see Fig. 1). Baseline cigarette smoking rate will be established over days 1-5. After overnight smoking abstinence, a laboratory visit on day 6 will assess e-cigarette flavor-associated subjective reward, affect, craving relief, and withdrawal relief. After overnight smoking abstinence, a laboratory visit on day 7 will assess the reinforcing value of the assigned e-cigarette flavor relative to combustible cigarettes.

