#### Data analysis

3.10.2

Prior to analyses, the data will be screened for entry errors and outliers, the extent and type of missing data will be assessed, and the most appropriate method for dealing with the missing data will be selected. For Aim 1, longitudinal cigarette counts (normalized as percent of baseline) will be analyzed using mixed models (Gaussian family) in the primary analysis. The model will include predictors of time (continuous or discrete), study phase (baseline, switch period, or follow-up), flavor group, candidate covariates, and predictors (e.g., e-cigarette use). It will be tested using the z-scores corresponding to the study phase by flavor group interaction terms with fruit-flavored as the reference. For an intent-to-treat (ITT) analyses, ITT will be defined as those randomized to a flavor group at day 6.

For Aim 2, measures are summary scores and difference scores and will be addressed using multiple regression methods. We will first test whether participants randomized to fruit versus tobacco or menthol-flavored e-cigarettes report greater subjective reward, greater increases in positive affect, and have a higher relative reinforcing value of e-cigarette flavoring using the t-score associated with the group difference. We will then test whether these effects predict fewer cigarettes smoked per day during the 6-week switching phase and at the 26-week follow-up.

Next, we will evaluate whether subjective reward, positive affect, and relative reinforcing value for entry into a model as predictors of change in cigarettes smoked per day (mean switch phase or follow-up cigarettes minus mean baseline cigarettes), using the significance of the corresponding t-score while controlling for craving, withdrawal, and negative affect relief. The series of regressions will occur within a structural equation model, with the effects of flavor (predictor) on cigarettes per day (outcome) across the switch follow-up phases mediated by subjective reward, positive affect, and the relative reinforcing value of flavor. We will compute the proportion of mediation for the indirect effects and evaluate the mediated paths for significance using the delta method and bootstrapped standard errors [[68], [69], [70]].

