The study focuses on AWS who have tried repeatedly, but unsuccessfully, to quit smoking. While this may lessen generalizability, this population is most suited to a harm-reduction approach [7,16,19]. These AWS have not been successful with medication and their likelihood of quitting is less when the same medication is used on sequential attempts [72]. With only three medications approved by the FDA over the past five decades, these individuals have few options. Research indicates adults are turning to e-cigarettes more frequently than any other medicinal smoking cessation product [73].

If the hypotheses are supported, it would suggest that the unavailability of fruit-flavoring in e-cigarettes would unintentionally support continued combustible cigarette smoking among adults who have not been able to quit using traditional approaches. The findings may help to catalyze thinking surrounding the need for regulatory precision (e.g., moving all non-medicinal nicotine to adult retail outlets) rather than a complete flavor ban [19,71,74] to protect youth from using e-cigarettes while promoting use among smokers unable to quit smoking otherwise. If the hypotheses were not supported, it would suggest that fruit-flavored e-cigarettes do not confer an advantage over traditional flavors for smoking cessation and that their absence from the market does not negatively affect AWS who want to quit through e-cigarette use.

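### Free improvement: the stated 80% is the power of one pairwise comparison; beating both marketed flavors has about 70% power under the Bonferroni split, and a Hochberg rule lifts this to about 79% at no cost in participants

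*Protocol article*

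**What the plan says.** Section 3.10.1 (Sample size) sets the Aim 1 error rate and power: "hypotheses will be tested with 80% power using 5% two-sided alpha Bonferroni corrected to 2.5% for two group comparisons". It gives 70 per group and a detectable difference of about 3.73 CPD. In the Aim 2 paragraph of the same section: "The actual standard deviation for the cigarette consumption change score is 7.1".

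Section 3.10.2 (Data analysis) tests the "study phase by flavor group interaction terms with fruit-flavored as the reference". That gives two contrasts, fruit against tobacco and fruit against menthol.

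Section 2 (Aims and hypotheses) predicts more switching with fruit "than participants randomized to tobacco-flavored or menthol-flavored e-cigarettes". The Abstract says the trial will show "if fruit-flavored e-cigarettes facilitate initial and sustained switching more than menthol or tobacco".

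Section 4 (Discussion) says that if the hypotheses hold, "it would suggest that the unavailability of fruit-flavoring in e-cigarettes would unintentionally support continued combustible cigarette smoking among adults". If they do not, it infers that fruit has no advantage over the traditional flavors. It describes no third case in which fruit beats one flavor but not the other. The Introduction says that the sales ban left out tobacco and menthol, and section 3.7 describes both as widely available.

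**The concern.** A smoker who loses access to fruit pods can still buy tobacco or menthol pods. If one of these works as well as fruit, the loss of fruit need not keep that person smoking. The Discussion's conclusion is therefore best supported when fruit is better than each of the two flavors.

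A Bonferroni split is designed for separate claims against each comparator. A claim that requires both contrasts to succeed does not need it, so the split spends power on protection that the claim does not use. The single power figure of 80% also leaves the reader without the probability of reaching the conclusion that matters most. At stake are about ten points of power for the main policy statement, and a clear meaning for a mixed result.

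**Working it through.** **Inputs.** n = 70 per arm, 1:1:1 (section 3.1); difference 3.73 CPD, two-sided 2.5% per contrast, 80% power (section 3.10.1). The SD of 7.1 is stated under Aim 2; applying it to Aim 1 is an assumption, supported by step 1.

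**1. Reproduce the stated figure.**
- Standard error of a difference = 7.1 × √(2/70) = 1.200.
- Standardized difference = 3.73 / 1.200 = 3.108.
- Two-sided critical values: 2.241 at 2.5%, 1.960 at 5%.
- Power of one contrast at 2.5% = Φ(3.108 − 2.241) = Φ(0.867) = 80.7%. By the noncentral t with 138 df it is 79.9%, and the detectable difference at 80% power is 3.73 CPD.

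The stated 80% is the power of one comparison.

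**2. Power to beat both.** The two contrasts share the fruit arm, so with equal arms and equal variances their correlation is 0.5. With both true differences at 3.73 CPD, power is the bivariate normal probability that both statistics exceed the critical value:
- each at 2.5% (as written): Φ₂(0.867, 0.867; 0.5) = 69.7%;
- each at 5%: Φ₂(1.148, 1.148; 0.5) = 79.4%.

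Power for at least one win at 2.5% each is 91.7%, so the 80% is not the either-win power. To reach 80% for both wins with the split would take 85 per arm (255 evaluable); with each test at 5% it would take 71 per arm (213 evaluable).

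**3. Error of a both-wins claim.** The worst case is one true null beside a very large effect on the other contrast. The chance of wrongly claiming both wins in fruit's favor is then 0.025/2 = 1.25% with the split and 0.05/2 = 2.5% with each test at 5%. The split is stricter than needed.

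**4. Hochberg rule.** Declare both contrasts if both two-sided p ≤ 0.05; otherwise declare only a contrast with p ≤ 0.025. Both contrasts are declared exactly when both p ≤ 0.05, so both-wins power is the 79.4% of step 2. Simulated familywise error (4 million draws, two-sided) is 4.8% with both nulls true and 4.4% with menthol equal to fruit and tobacco worse by 3.73 CPD. It reaches 5.0% in the limit of a very large tobacco effect. Every contrast that Bonferroni rejects, Hochberg also rejects, so no power is lost.

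**5. Sensitivity.** With the tobacco difference at 3.73 CPD and an assumed smaller menthol difference, both-wins power is:

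| Menthol difference (CPD) | Bonferroni | Hochberg |
|---|---|---|
| 3.73 | 69.7% | 79.4% |
| 3.0 | 54% | 66% |
| 2.5 | 41% | 52% |
| 2.0 | 27% | 37% |

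**The case against.** A reader might infer that a win over either flavor is enough for the policy conclusion, and that its error is therefore uncontrolled. If fruit equals menthol and tobacco is worse by 3.73 CPD, at least one contrast favors fruit in about 81% of trials. The documents do not support that charge. No passage makes one win sufficient, and the wording of the hypotheses can be read as requiring both. Bonferroni controls familywise error whichever nulls are true, so each pairwise claim stays valid. The 81% is essentially the power of a correct rejection of fruit versus tobacco.

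A reader might also say that the plan promises 80% joint power and fails to deliver it. It does not promise that: a detectable pairwise difference at a corrected level is a conventional and correct statement.

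Two further objections have some force. The Discussion's sentence is hedged and is not a formal decision rule. The need to beat both flavors is also a reasonable argument rather than a strict entailment: if some people who lost fruit took up tobacco instead of menthol, the loss could matter even with menthol as good as fruit. Finally, Hochberg relaxes the threshold when both contrasts reach 5%, in a registered trial with open assignment, so the change is more than editorial.

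These points remove any charge of error inflation. They leave standing that a method with the same familywise guarantee and no less power is available. The alpha rule, the power and the inference are all stated in the article, so this is not a complaint about detail left to another document.

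**Conclusion.** This is a free improvement, not the repair of an invalid test. The plan's 80% is correct for a single comparison. For the conclusion in the Discussion, which is best supported by superiority over both flavors, power is about 70% under the split and about 79% under Hochberg, with the same 70 per arm and familywise error still at 5%.

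The figures assume an SD of 7.1 for Aim 1, normal test statistics, equal variances and both true differences at 3.73 CPD. They are on raw CPD change, whereas the primary analysis is a mixed model of percent of baseline. They therefore check the stated 3.73 CPD and do not give the power of that model. The gain over Bonferroni holds across the assumed menthol differences, but no choice of multiplicity rule makes the trial well powered for both wins if the menthol difference is well below 3.73 CPD.

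**What to change.** 1. In sections 3.10.1 and 3.10.2, replace the Bonferroni split with the Hochberg rule: if both contrasts have two-sided p ≤ 0.05, declare both; otherwise declare only a contrast with p ≤ 0.025 and limit the claim to that comparator. Superiority requires the difference to favor fruit. Note that the positive correlation from the shared fruit arm supports familywise control at 5%.
2. In the Discussion, say that the conclusion about unavailability of fruit flavors will be drawn only if fruit is superior to both tobacco and menthol. This also settles what a mixed result means.
3. Restate the power as about 80% per comparison at 2.5% and about 79% for beating both at 3.73 CPD each, falling to about 37% to 66% if the menthol difference is assumed to be 2.0 to 3.0 CPD.

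The cost is a dated amendment, made before anyone sees outcome data by arm. No participants, visits or data are added. The one concession is that a win over a single flavor would no longer support the general policy statement.

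### Single-step Bonferroni for the two Aim 1 fruit contrasts is valid, but Holm's step-down gives more power at the same 5% family-wise error for one line of wording

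*Protocol article*

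**What the plan says.** Section 3.10.1 (Sample size) of the protocol article states for Aim 1 that "hypotheses will be tested with 80% power using 5% two-sided alpha", and that this level is "Bonferroni corrected to 2.5% for two group comparisons". Section 3.10.2 (Data analysis) identifies the tests as the "study phase by flavor group interaction terms with fruit-flavored as the reference", so the two comparisons are fruit versus tobacco and fruit versus menthol, with the fruit arm in both.

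Section 3.10.1 gives about 3.73 CPD as the difference that 70 per group can detect. It also states the direction: "We expect the initial and sustained switch for participants randomized to fruit-flavoring to be greater than for participants randomized to tobacco or menthol flavoring". No step-down or other sequential procedure is mentioned, and no reason is given for the single-step form. The Bonferroni sentence is confined to Aim 1; no correction rule is written for the Aim 2 measures.

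**The concern.** Bonferroni holds each contrast to 2.5% whatever the other one shows. Holm tests the smaller p-value at 2.5% and, only if that is significant, tests the larger at 5%. Every Bonferroni rejection is also a Holm rejection, and the family-wise error stays at or below 5% whatever the correlation between the tests, so the shared fruit arm causes no difficulty.

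What is at stake is power for the second contrast. The article expects fruit to do better than each of the two other flavors. If that is true, the weaker contrast is the one most likely to fall between the 2.5% and 5% thresholds, and Bonferroni would leave it unclaimed although the family-wise error would allow the claim.

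**Working it through.** **Inputs**
- 70 per arm, 1:1:1 allocation (sections 3.1 and 3.10.1).
- Two-sided 2.5% per comparison, 80% power (section 3.10.1).
- Difference 3.73 CPD. The article presents this as a detectable difference, not as an expected effect.
- SD 7.1 CPD: "The actual standard deviation for the cigarette consumption change score is 7.1". This stands under Aim 2. That it also applies to the Aim 1 difference is an assumption, because no SD is given there.
- Two-sample comparison of means. This too is an assumption: the planned model is a mixed model on counts expressed as percent of baseline.

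**Reproducing the stated figure**

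Standard error = 7.1 × √(2/70) = 1.200.

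Detectable difference (normal) = 1.200 × (2.241 + 0.842) = 3.70 CPD. With the noncentral t distribution it is 3.734 CPD, which agrees with the stated 3.73. At 5% it would be 3.36 (normal) or 3.39 (t), so the stated figure does use 2.5%, and the SD of 7.1 fits it.

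Power at 3.73 under Bonferroni: 3.73/1.200 = 3.108, and Φ(3.108 − 2.241) = 0.807. The noncentral t gives 0.799.

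**Bonferroni against Holm**

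With equal arms and a shared fruit arm, the two test statistics have correlation (σ²/n)/(2σ²/n) = 0.5. The rules are:
- Bonferroni rejects contrast i if |Zᵢ| > 2.241.
- Holm rejects contrast i if |Zᵢ| > 2.241, or if |Zᵢ| > 1.960 and the other |Zⱼ| > 2.241.

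Results from 4 million simulated pairs of normal statistics, 70 per arm (2.8 is 75% of 3.73, rounded):

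| True differences (CPD) | Quantity | Bonferroni | Holm |
|---|---|---|---|
| 3.73 and 3.73 | each contrast | 80.8% | 85.2% |
| | both | 69.8% | 78.7% |
| | at least one | 91.7% | 91.7% |
| 3.73 and 2.8 | first contrast | 80.8% | 82.9% |
| | second contrast | 53.7% | 62.5% |
| | both | 49.0% | 59.9% |
| | at least one | 85.5% | 85.5% |
| 3.73 and 0 | true effect | 80.8% | 80.9% |
| | false rejection of the null contrast | 2.5% | 4.3% |
| 5 and 0 | false rejection of the null contrast | 2.5% | 4.8% |
| 0 and 0 | family-wise error | 4.7% | 4.7% |

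At least one success is equally likely under both methods by construction, because Holm's first step is the Bonferroni test. The entire gain is in the other contrast. The family-wise error stays below 5% in every row with a true null.

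**The case against.** The strongest objection is that this is a preference. Bonferroni is valid and prespecified, the sample size agrees with it, and the planned 80% power per comparison is met without Holm. It also comes with matching simultaneous 97.5% intervals, which Holm does not. All of this stands, and it is why the point is a suggestion and not a correction.

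A reader might infer that the trial succeeds only if fruit beats both flavors, so that the rise from 70% to 79% measures the loss. The article does not define success that way. It speaks of tobacco or menthol and corrects for two comparisons, which fits two separate claims. If a single claim did require both tests, no correction would be needed: each could be tested at 5%, with about 79.4% power for both, slightly more than Holm's 78.7%. For separate claims the relevant gain is the one per comparison, about 4.5 points when both differences are 3.73 CPD.

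A reader might also infer that Bonferroni is prescribed for Aim 2. It is not written there. The Aim 2 detectable differences are consistent with 2.5%: the t-based standardized difference of 0.526 gives 0.526 × 7.0 = 3.68 for positive affect (stated about 3.7) and 0.526 × 1.3 = 0.68 for subjective reward (stated 0.68), against 3.34 and 0.62 at 5%. Agreement of figures is not a stated testing rule.

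Finally, the absolute powers depend on a borrowed SD and a simplified model. That limits the percentages. It does not affect the ordering of the two methods, which holds on any scale.

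**Conclusion.** The point holds as an optional efficiency gain. For the two Aim 1 contrasts, Holm keeps the 5% family-wise error and adds about 4 to 5 points of power per comparison if both true differences are 3.73 CPD, and about 9 points for a second contrast 75% as large. It does nothing for the chance of at least one success and almost nothing if one effect is zero. These sizes assume an SD of 7.1 CPD for the Aim 1 difference, 70 analysed per arm, and a two-sample approximation to the mixed-model interaction test. They do not show that the plan is underpowered or its error control faulty.

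**What to change.** In section 3.10.1, for the two Aim 1 primary contrasts, replace the Bonferroni wording with: *Holm step-down at an overall two-sided 5%*. Fix this before outcome data by arm are analysed. Keep 70 per arm, and keep the stated detectable differences, which become conservative.

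The cost is one line of wording and one reporting point: if 97.5% intervals are kept, an interval may include zero for a contrast that is significant at the second Holm step. Say so where the intervals are described.

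If the sponsor does apply a two-contrast correction to the Aim 2 measures, state that rule; the same substitution can then be made there.

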### Participant eligibility

3.2

Study participants (≥21 years old) will be 210 male and female adults who have persistently smoked cigarettes and are motivated to switch from combustible cigarettes to e-cigarettes. Persistent smokers are defined as those who have repeatedly tried to quit and failed to quit, even with the use of smoking cessation medication. To be eligible, potential participants must: (1) be English speaking; (2) report having smoked at least 5 cigarettes per day for the past 6 months and ever use of an e-cigarette; (3) have a CO ≥ 10 ppm; (4) be willing to switch to e-cigarettes for 6 weeks and use the assigned flavors.

Exclusion from study participation will be warranted due to: (1) regular use of any nicotine-containing products other than cigarettes; (2) regular e-cigarette use defined as ≥ 5 days/30 days; (3) current or impending (during study period) enrollment in a smoking cessation program; (4) current use of smoking cessation medication; (5) allergies to either propylene glycol or flavor additives; (6) current use of recreational drugs (other than nicotine and cannabis), current treatment for substance use, and alcohol use exceeding 20 standard drinks per week; (7) current or planned pregnancy or lactation; (8) history or current diagnosis of psychosis; and (9) serious or unstable disease in the past year (e.g., cancer, cardiovascular event).

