#### Missing data and dropout

3.10.3

We anticipate approximately 15% of the original 240 participants will drop out by week 26. The primary analysis of Aim 1 will be all available data, which may include some intermittent missingness, and some dropout. Because we cannot determine the cause of missingness, we will follow the primary analysis with a sensitivity analysis, looking for evidence of bias in our estimates revealed by the application of various data models. Those models will include (1) completers only, (2) last observation carried forward, (3) missing equals return to baseline smoking, and (4) multiple imputation using the MICE method.

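### The protocol uses 210 (70 per arm) both as the number randomised and as the number completing week 26 out of about 240; with about 15% dropout it cannot be both

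*Protocol article*

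**What the plan says.** Two sections of the protocol article give 210 as the trial's size. Section 3.1 (Overview of study design) places the comparison "among 210 adults who have persistently smoked cigarettes" and assigns them 1:1:1, with 70 in each of the fruit, tobacco and menthol arms. Section 3.2 (Participant eligibility) says that the study participants "will be 210 male and female adults who have persistently smoked cigarettes".

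Two other sections start from 240. Section 3.10.1 (Sample size) allows for about 15% attrition by enrolling about "240 participants to have 210 who complete the 26-week follow-up". Section 3.10.3 (Missing data and dropout) expects that approximately "15% of the original 240 participants will drop out by week 26".

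The power statements in section 3.10.1 all rest on 210, or 70 per group: "A sample of 210 (70 per group) will allow us to detect an overall standardized slope of 0.19", and "A sample of 70 per group enables us to detect a difference of" about 3.73 CPD. The test level is "5% two-sided alpha Bonferroni corrected to 2.5% for two group comparisons", and the "hypotheses will be tested with 80% power".

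Three further statements bear on the reading. Section 3.10.2 (Data analysis) defines the intent-to-treat set as those randomised to a flavour at day 6. The primary outcome runs to day 49, with week 26 secondary. The primary Aim 1 analysis uses all available data, and completers-only is a sensitivity analysis.

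**The concern.** The number randomised is a basic design parameter, and here it has two values. In sections 3.1 and 3.2, 210 is the number allocated to arms. In section 3.10.1 it is what remains after 26 weeks of attrition. Both could hold only if nobody dropped out after randomisation, yet section 3.10.3 expects dropout and plans four sensitivity models for missing data.

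Two things depend on the answer. The first is the intent-to-treat denominator, which is 210 on one reading and about 240 on the other. The second is the number of participants with week-26 data. The detectable difference of 3.73 CPD is stated for 70 per group. If 70 per arm are only randomised, fewer than 70 will be observed at week 26, the endpoint that carries the sustained-switching hypothesis in the aims section.

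**Working it through.** **Inputs.** From section 3.10.1: two-sided alpha 0.025 per comparison, 80% power, 70 per group, detectable difference about 3.73 CPD, attrition about 15%, enrolment about 240, week-26 completers 210. From section 3.1: 70 randomised per arm. The SD of 7.1 is given in the Aim 2 paragraph of section 3.10.1 for the change in cigarette consumption. Applying it to the Aim 1 figure is an assumption, tested in step 1.

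**Step 1: reproduce the stated detectable difference.** For two means with n per arm, the two-sided t test at alpha 0.025 has noncentrality (difference / SD) × √(n/2).
- At n = 70, 80% power needs a standardised difference of 0.5259, and 0.5259 × 7.1 = 3.73 CPD.
- Conversely, a difference of 3.73 gives 3.73/7.1 × √35 = 3.11, and power of 79.9%.

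The stated figure reproduces at 70 evaluable per arm. The match supports using the SD of 7.1.

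**Step 2: the retention arithmetic.**
- 240 × 0.85 = 204, or 68 per arm.
- 210 / 0.85 = 247.06, so 248 enrolled would leave 210 at exactly 15% loss.
- 1 − 210/240 = 12.5%, the loss at which 240 yields exactly 210.
- 210 × 0.85 = 178.5, or 59.5 per arm, if 210 is the number randomised.

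**Step 3: power for 3.73 CPD at week 26 under each reading.** Same t test, SD 7.1, alpha 0.025, using only participants observed at week 26.

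| Reading | Per arm at week 26 | Detectable difference (80% power) | Power for 3.73 CPD |
|---|---|---|---|
| As stated | 70 | 3.73 CPD | 79.9% |
| 240 randomised, 15% lost | 68 | 3.79 CPD | 78.6% |
| 210 randomised, 15% lost | 59.5 | 4.06 CPD | about 72% |

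A normal approximation gives slightly higher power: 80.7%, 79.4% and 73.4% in the same order. The differences between rows are much the same.

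**Step 4: which endpoints this touches.** Dropout by week 26 acts on the week-26 comparison. By day 49 less of it should have occurred; the protocol gives no attrition figure for that time, so no power is computed for it here. Subjective reward and positive affect are measured on day 6 and relative reinforcing value on day 7, before the switch phase, so week-26 dropout does not reduce those group comparisons.

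**The case against.** **The power section addresses attrition itself.** Section 3.10.1 gives the enrolment target, section 3.10.3 repeats it, and sections 3.1 and 3.2 can be read as summaries. This stands in part: the 72% figure applies only if 210 really is the number randomised. But section 3.1 gives an allocation of 70 to each arm, which is a specific statement and not a loose summary.

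**240 may be enrolled at intake and 210 randomised later.** Consent is at day 0 and the intent-to-treat set is fixed at day 6, so the two counts can differ. This does not reconcile the text, because 210 is tied to completing the 26-week follow-up and the 15% loss is placed by week 26. It does mean that 240 as the randomised total is an inference. The protocol calls these participants enrolled and original, and nowhere says that 240 are randomised.

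**A reader might infer that the stated power does not follow from the stated size.** The document does not support that. At 70 evaluable per arm the 3.73 CPD figure reproduces. At 68 per arm the cost is about 1.3 points of power (79.9% against 78.6%).

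**A reader might also treat 204 against 210 as a serious inflation error.** Section 3.10.1 marks both 240 and 15% as approximate. The gap is 6 of 210, or 2.9%. Multiplying instead of dividing (210 × 1.15 = 241.5) may be how 240 arose. This part alone changes no design decision.

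**Week 26 is secondary.** The primary comparison ends at day 49, and the mixed model uses all available data, so participants lost before week 26 still contribute. This stands, and it limits how far the problem reaches.

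**Conclusion.** Wrong as written, of modest severity. The protocol gives 210 two incompatible meanings, and the conflict is visible in its own text whatever the full protocol or analysis plan adds.

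The consequence depends on which meaning is operative. If about 240 are randomised, the effect is about one point of power at week 26. If only 210 are randomised, power for 3.73 CPD at week 26 falls by 7 to 8 points, to about 72%. That result assumes 15% loss spread evenly over the arms, the SD of 7.1, and a comparison of participants observed at week 26.

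Two stronger conclusions do not follow. The primary day-49 endpoint is not shown to be underpowered, since its loss should be smaller and the protocol gives no attrition figure for it. The Aim 2 detectable group differences of 3.7 for positive affect and 0.68 for subjective reward are not weakened by week-26 dropout, since both are measured on day 6.

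**What to change.** State one randomised total and use it in sections 3.1, 3.2, 3.10.1 and 3.10.3. If 240 is the number randomised, sections 3.1 and 3.2 should read about 240, 80 per arm, and 210 should be labelled throughout as the approximate week-26 completer target. If 240 instead counts people enrolled before randomisation, say so, give the number randomised separately, and restate the week-26 completers and power from that number.

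As a minor correction, make the retention figures agree. Either give expected completers as about 204 (68 per arm, detectable difference about 3.8 CPD), or state the attrition assumption as 12.5%.

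If about 240 is already the randomisation target, the cost is a text correction only. No enrolment beyond 240 is needed. If 204 is adopted, the stated detectable difference at week 26 becomes slightly less favourable.
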